## Abstract

Aging is characterized by substantial changes in sleep architecture that negatively impact fitness, quality of life, mood, and cognitive functioning. Older adults often fail to reach the recommended level of physical activity to prevent the age-related decline in sleep function, partly because of geographical barriers. Implementing home-based interventions could surmount these obstacles, thereby encouraging older adults to stay active, with videoconference administration emerging as a promising solution. Increasing the availability of biological rhythms synchronizers, such as physical activity, light exposure, or vestibular stimulation, represents a viable non-pharmacological strategy for entraining circadian rhythms and potentially fortifying the sleep–wake cycle, thereby enhancing sleep in aging. This study aims to (1) assess the impact of remote physical exercise training and its combination with bright light exposure, and (2) investigate the specific contribution of galvanic vestibular stimulation, to sleep quality among healthy older adults with sleep complaints. One hundred healthy older adults aged 60–70 years with sleep complaints will be randomly allocated to one of four groups: a physical exercise training group (*n* = 25), a physical exercise training combined with bright light exposure group (*n* = 25), a galvanic vestibular stimulation group (*n* = 25) or a control group (i.e., health education) (*n* = 25). While physical exercise training and health education will be supervised via videoconference at home, bright light exposure (for the physical exercise training combined with bright light exposure group) and vestibular stimulation will be self-administered at home. Pre-and post-tests will be conducted to evaluate various parameters, including sleep (polysomnography, subjective questionnaires), circadian rhythms (actigraphy, temperature), fitness (physical: VO_2_ peak, muscular function; and motor: balance, and functional mobility), cognition (executive function, long-term memory), quality of life and mood (anxiety and depression). The findings will be anticipated to inform the development of recommendations and non-pharmaceutical preventive strategies for enhancing sleep quality in older adults, potentially leading to improvements in fitness, cognition, quality of life, and mood throughout aging.

## Introduction

1

Aging induces changes in various physiological functions, including shifts in sleep patterns (1–3). Older adults often report difficulties in falling and staying asleep, spending increased time awake during the night, and experiencing daytime sleepiness (3–5). The decline in sleep quality with age also significantly impacts the quality of life (QoL), defined as “the degree of need and satisfaction within the physical, psychological, social, and environmental domains” (6). Evidence indicates that impaired sleep quality is closely associated with adverse effects on physical and psychological well-being, as well as limitations in daily activities and cognitive functions (7). Thus, enhancing sleep quality in older adults becomes a crucial objective for maintaining QoL.

The sleep/wake cycle is influenced by both endogenous and exogenous components. The endogenous component corresponds to our central biological clock, located in the suprachiasmatic nuclei of the hypothalamus (8, 9). This autonomous system ensures the genesis, maintenance, and control of biological rhythms, such as body temperature or cortisol levels, which are involved in glucose homeostasis. The exogenous component refers to the external synchronizers in our environment that contribute to entraining biological rhythms over a given period. Synchronizers can either modify the phases (phase shifts) or synchronize the circadian rhythms (10). In humans, the most powerful synchronizer for the biological clock is the 24-h light/dark cycle (11, 12). The impact of light on the circadian clock depends on the timing of light exposure: early morning light exposure advances the clock, while evening and night light exposure delays it (13, 14). Previous studies have demonstrated that bright light exposure helps synchronize circadian rhythms and improve QoL, sleep, and cognitive parameters (15–17). Another non-photic synchronizer identified in the literature is physical activity (18, 19). Previous studies have reported that physical exercise training in individuals over 60 years helps synchronize endogenous circadian rhythms, supporting the idea that non-photic stimuli also act as synchronizers for the human circadian clock (20). Additionally, exercise has been associated with reductions in daytime sleepiness and improvements in sleep quality (21, 22). Exercise has also been shown to reduce the use of hypnotics in this population, which is significant given the adverse side effects of these drugs on cognition, executive function, and mobility (23, 24). Additionally, maintaining moderate physical activity for 25–65 min per day can eliminate the risk of mortality associated with sleep disorders (25). However, the timing of exercise can be crucial for enhancing sleep quality, yet a limited number of studies on this subject involving older adults have been conducted (26). Acute exercise in the morning has been shown to improve nocturnal sleep quality in older adults with difficulty initiating sleep, as assessed with polysomnography (27), while acute vigorous exercise ending ≤1 h before bedtime affects sleep quality and awakenings compared to a control group (no exercise) (26). To our knowledge, only one study has investigated the effects of chronic exercise in the morning or evening (for 14 days) in older adults using polysomnography, and it reported no objective changes in sleep (28). Finally, exercise in older adults is also of interest because of its numerous positive effects on QoL, physical condition, and cognition (29–32). While bright light exposure and exercise are essential for the synchronization of circadian rhythms and significantly contribute to overall sleep quality, the effects of combined light and exercise exposures on sleep quality are not yet well known.

Unfortunately, one in three older adults fails to meet the recommended levels of physical activity (33), resulting in missed health benefits (33). Giné-Garriga et al. (34) showed that older adults allocate 78.8% of their waking time to sedentary behavior, 18.6% to light-intensity physical activities, and only 2.6% to moderate-to-vigorous physical activities. Seniors often cite barriers such as the cost of sports sessions or the distance between home and sports facilities (35, 36). Home-based remote supervised interventions could overcome these limitations and improve overall health (37–39). Videoconferencing technology can facilitate interactions between the participants and the physical trainers, providing a pragmatic alternative to face-to-face home visits by physical trainers (37–39). Several studies have demonstrated that digital platforms exhibit high rates of adherence, compliance, and satisfaction among older participants (37, 40). Additionally, videoconferencing has been shown to achieve the same benefits as face-to-face programs (41), making it an optimal solution. To our knowledge, this study is the first to evaluate the effects of various home-based interventions using videoconference and a digital monitoring platform on sleep quality in healthy older adults with sleep complaints.

All motor activities require the integration of sensory information. During exercise, the brain continuously processes sensory input to maintain balance, head position, and spatial orientation. This sensory information is handled by the vestibular system, located within the inner ear. Recent studies conducted in both animals and humans have suggested a link between the vestibular system and circadian rhythms (42, 43), suggesting that vestibular stimulation could serve as a synchronizer with potential positive impacts on sleep. Only a few studies have investigated the effects of vestibular stimulation on sleep. These studies have used vestibular stimulations induced by rocking movements or galvanic currents (i.e., a non-invasive method that stimulates the vestibular nerve using a direct low-intensity electrical current) (44–46). Polysomnography, a gold standard method (47), was used to record sleep in these studies. Research on rocking movements demonstrated improvements in sleep/wake transitions and alterations in electroencephalographic activity during nights or naps experienced on a moving bed compared to a stationary one (44, 45). Only one study, employing a specific model involving an advance in bedtime by 4 h, has explored the effects of galvanic vestibular stimulation on sleep in a specific population (insomniacs), which revealed a reduction in persistent sleep latency (46). However, the effects of galvanic vestibular stimulation on the sleep of older adults under ecological conditions (without phase advance) remain to be evaluated. Galvanic vestibular stimulation emerges as an innovative and easily administered technique, presenting an interesting prospect for resynchronizing circadian rhythms and improving sleep.

The aims of this study are (1) to evaluate the effects of remote physical exercise training and the combined effects of remote physical exercise training and bright light exposure on sleep quality in healthy older adults with sleep complaints, and (2) to study the specific contribution of galvanic vestibular stimulation on sleep quality in the same population. By reinforcing circadian rhythms, the various interventions should improve sleep quality, physical and motor fitness, cognition, and, consequently QoL.

## Materials and methods

2

### Study design

2.1

The study is a randomized controlled trial with four parallel groups: a Physical Exercise Training group (PET), a PET combined with Bright Light Exposure group (PET + BLE), a Galvanic Vestibular Stimulation group (GVS), and a control group [Health Education (HE)]. All participants will be provided written informed consent before their inclusion. The protocol has been approved by the local ethical committee (Comité de Protection des Personnes, CPP Nord Ouest III, Caen) in compliance with French regulations (trial registration number: IDRCB: 20206A01578-31). The researchers will provide participants with detailed written and oral information about the trial, ensuring voluntary participation and emphasizing that participants may withdraw at any time.

### Participant

2.2

Participants will be recruited through advertisements in the local newspapers and media reports. One hundred healthy retired participants, both male and female, aged between 60 and 70 years and independently living in Normandy, will be enrolled. Exclusion criteria will include: not having computing equipment (computer, web connection and webcam), signs of cognitive impairment reflected by a Mini-Mental State Examination (MMSE) score below 26/30 (48), no sleep complaint reflected by a Pittsburgh Sleep Quality Index (PSQI) score > 5 (49), extreme circadian typology reflected by the Morningness-Eveningness Questionnaire (MEQ) (50) score below 31 or above 69, uncontrolled psychiatric, vestibular, neurologic, endocrine or cardiovascular affections, uncorrected hearing and/or visual impairment, psychotropic or bradicardizing medical treatments, alcohol, drug or caffeine abuse, and recent hospitalization (<30 days), all to be assessed by medical evaluations and screenings. Participants ranking moderately or highly active according to the International Physical Activity Questionnaires (IPAQ) (51) will be excluded. The ability to engage in moderate to vigorous physical activity will be assessed by a medical examination and cardiac screening during a maximal incremental test (VO_2_ peak) on a cycle-ergometer (detailed below), supervised by cardiologists at the sports medicine department of the local hospital of CHU in Caen. Complete inclusion and exclusion criteria are listed in Table 1. Eligible participants will be allocated to one of four groups using simple randomization from a computer-generated numbered sequence with 25 blocks of 4, to be conducted by researchers. Participants will be assigned a number in the order of their registration inclusion in the study.

**Table 1 tab1:** Inclusion and exclusion criteria.

Inclusion criteria	Exclusion criteria
Participant ≥60 ≤ 70 y.o Retired for ≥12 months Good health condition Living in Normandy Sedentary behavior Sleep complaints reflected by a PSQI score > 5 Computing equipment Satisfactory cardiac screening	Cognition <26/30 on the MMSE IPAQ = moderately and highly active Circadian typology = extreme chronotype Sign of cognitive impairment Uncontrolled psychiatric, vestibular, neurologic, endocrine or cardiovascular affections Uncorrected hearing and/or visual impairment Psychotropic or bradicardizing medical treatments Recent hospitalization (<30 days) Alcohol, drug or caffeine abuse

### Assessments

2.3

Inclusion and randomization will occur at the baseline assessment (visit 1) and will involve the completion of pre-inclusion questionnaires. A pre-intervention visit will take place before the start of the intervention (visit 2) and a 12-week follow-up assessment will occur at the end of the 12-week intervention (visit 3) (Figure 1A). A final assessment will be performed after completion of the 14-week intervention, but only for control and GVS groups (visit 4) (Figure 1B). According to the literature, a typical GVS protocol is short and does not exceed 2 weeks (52). Therefore, the GVS protocol will be shorter than PET and BLE interventions to ensure participant feasibility and acceptability. The two weeks of vestibular stimulation will be scheduled after the 12-week follow-up to ensure consistent design (Figure 1B). The control group will be compared to the PET and PET + BLE group, but also to the GVS group.

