**Figure 1 fig1:**
[figure not shown]
Participant’s flow chart. **(A)** The first part of participant’s flow chart: PET and PET+BLE interventions; **(B)** the second part of participant’s flow chart: GVS intervention. PET, Physical Exercise Training; BLE, Bright Light Exposure; HE, Health Education; GVS, Galvanic Vestibular Stimulation.

Sleep, circadian rhythms, physical and motor fitness, cognitive, QoL, and mood measurements will be assessed during visits 2, 3, and 4, by researchers in our laboratory. The VO_2_ peak test will be performed during visits 2 and 3 only for PET, PET + BLE, and control groups (not for the GVS group, which will not engage in physical exercise) and will allow the exclusion of participants with cardiac disorders. These tests will be conducted by cardiologists at the sports medicine departments of the local hospital of CHU in Caen. The content of all assessments is described in Figure 1.

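### Apart from the screening PSQI, the pre-intervention outcomes are measured after randomisation, at a visit whose content already depends on the arm, so self-reported and effort-dependent baselines can be shifted by knowledge of allocation

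*Protocol article*

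**What the plan says.** Section 2.3 (Assessments) places allocation at the first visit: "Inclusion and randomization will occur at the baseline assessment (visit 1) and will involve the completion of pre-inclusion questionnaires". A separate pre-intervention visit, visit 2, follows before any intervention begins. The outcome domains are then assigned to later visits: "Sleep, circadian rhythms, physical and motor fitness, cognitive, QoL, and mood measurements will be assessed during visits 2, 3, and 4". Visit 1 is not in that list.

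Visit 2 is not the same for everyone: "The VO_2_ peak test will be performed during visits 2 and 3 only for PET, PET + BLE, and control groups". The same sentence says that this test "will allow the exclusion of participants with cardiac disorders".

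Section 2.2 (Participant) describes the order differently. It treats the cycle-ergometer test as part of the medical check on fitness to exercise, lists satisfactory cardiac screening among the inclusion criteria in Table 1, and then states: "Eligible participants will be allocated to one of four groups using simple randomization from a computer-generated numbered sequence with 25 blocks of 4, to be". One sleep score must exist before allocation, because Table 1 also requires "Sleep complaints reflected by a PSQI score > 5".

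Section 2.7 (Statistical analyses) compares the groups by repeated measures ANOVA on pre and post values. One ANOVA covers exercise (PET), exercise plus light (PET + BLE) and control; a second covers GVS and control.

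**The concern.** In a pre/post analysis the baseline protects the comparison only if allocation could not have influenced it. Here the baseline is taken after allocation, and the arms are exercise classes, exercise with a lamp, mastoid electrodes or weekly health education. A participant who knows the arm cannot mistake it for another.

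The exposed measures are those that depend on report or effort: ISI, ESS, sleep diary, the repeat PSQI, SF-36, the anxiety and depression scales, grip strength, leg power and VO2 peak. Someone who has drawn health education might report worse sleep or push less hard than someone who has drawn an active arm, or the reverse. The ANOVA would treat the resulting gap as a genuine pre-intervention difference and carry it into the change contrast. Section 2.6 bases the sample size on sleep quality, which is partly self-reported. This affects the baselines of everyone retained, and is a separate matter from who is excluded by the cardiac test.

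**Working it through.** **Order of events.** Set side by side, section 2.3 gives: visit 1, randomisation; visit 2, first outcome measurement; then the intervention. The arm-specific VO2 peak test at visit 2 can be scheduled only by someone who knows who is in GVS, so allocation is in use by then. Section 2.2 has researchers carry out the randomisation and section 2.3 has researchers carry out the assessments.

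**The plan's own figure.** Section 2.6 gives f = 0.4, α = 0.05 and a value of 0.90 (read as power), leading to 24 per group. For a four-group one-way ANOVA the noncentrality is λ = f² × k × n = 0.16 × 4 × 24 = 15.36 on 3 and 92 degrees of freedom. Power is 0.912, and 24 is the smallest n that reaches 0.90, so the figure reproduces. The point disputes no stated number, and changing the order leaves 24 per group as it is.

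**Bias.** Let knowledge of the arm shift one arm's baseline by b and its post value by c, in SD of a single measurement. The change contrast is then biased by c − b. If post values are unaffected (c = 0), the bias has size b; if the shift persists unchanged (c = b), it cancels.

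**Type I error.** Assumptions, none of them in the documents: no true effect, c = 0, a two-arm comparison of change scores, pre/post correlation r. The n of 25 per arm is the planned group size.

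- SD of change = √(2(1 − r))
- Noncentrality = b / [√(2(1 − r)) × √(2/n)], with 2n − 2 = 48 degrees of freedom
- For r = 0.5 and b = 0.2: SD of change = 1, √(2/25) = 0.283, noncentrality = 0.2/0.283 = 0.71, two-sided type I error = 0.107

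| b (SD) | r = 0.3 | r = 0.5 | r = 0.7 |
|---|---|---|---|
| 0 | 0.05 | 0.05 | 0.05 |
| 0.1 | 0.060 | 0.064 | 0.073 |
| 0.2 | 0.090 | 0.107 | 0.146 |
| 0.3 | 0.142 | 0.180 | 0.269 |
| 0.5 | 0.310 | 0.410 | 0.609 |

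The table is an unadjusted two-arm calculation. The plan's first ANOVA has three groups with Tukey comparisons, so the table shows the direction and order of the effect, not the plan's exact error rate. Baseline-adjusted analysis would not cure the problem: at r = 0.5 and b = 0.2 the bias would be r × b = 0.10 SD and the type I error 0.069.

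**The case against.** Much can be said on the other side.

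- **Disclosure is not stated.** The article does not say when participants learn their arm, and it is silent on blinding. It condenses a fuller protocol, and Figure 1, which lists the assessment content, is not available. A reader might infer that participants are told at visit 1; the text does not say so. This stands, and it makes the shift a possibility, not a fact. It does not change the stated order, or the need for staff to use the allocation at visit 2.
- **Not every baseline is affected.** A screening PSQI precedes allocation, and polysomnography is less exposed. Both stand. The article also calls visit 1 the baseline assessment, and section 2.5 separates baseline results from those before the intervention, but section 2.3 assigns no outcome measurement to visit 1.
- **The VO2 schedule reveals little.** PET, PET + BLE and control all take the test, so the schedule by itself marks out only GVS. This stands: for the first ANOVA, the exposure depends on allocation being known by some other route.
- **Section 2.2 suggests that cardiac screening comes first.** It does, and that contradicts section 2.3. The two need reconciling; neither can be taken as settled.
- **The GVS baseline may be visit 3.** Stimulation is given after the 12-week follow-up, and both GVS and control are measured at visits 3 and 4. This stands and limits the remedy.
- **The size is assumed.** A reader might divide a shift of 0.1 to 0.3 SD by d = 2f = 0.8 and report a bias of 12% to 38% of the planned effect. The documents do not support that. They give no shift, and f = 0.4 belongs to a four-group calculation. There d = 0.8 holds only for a two-against-two split. If one arm differs, d = 0.4/√(0.25 × 0.75) = 0.92; with two arms at opposite extremes and two midway, d = 0.4 × √8 = 1.13.

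**Conclusion.** The concern holds in a limited form. As section 2.3 is written, the pre values other than the screening PSQI are collected after allocation, at a visit that staff can run only by knowing who is in GVS, in a trial whose arms are distinguishable. That opens an avoidable route for bias in self-reported and effort-dependent baselines. The documents do not show that such bias will occur, and they do not establish that participants know their arm at visit 2.

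The size cannot be derived from the documents. Bias equal to the baseline shift requires unaffected post values; a persistent shift would cancel in part or in full. On the stated assumptions, 0.2 SD gives a type I error between 0.090 and 0.146 for correlations of 0.3 to 0.7. The point justifies a change because the remedy is cheap, not because a large bias has been shown.

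**What to change.** Amend section 2.3 so that inclusion and the screening questionnaires stay at visit 1, the outcome measures common to all four arms are completed at visit 2 (including the polysomnography night, the 7-day actigraphy and the temperature day), and the allocation is generated and disclosed to participants and staff only after the last of these. The wording should refer to the last common measure and not to completion of visit 2, because an arm-specific test cannot precede allocation.

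Reconcile sections 2.2 and 2.3 on whether the VO2 peak and cardiac screening test comes before allocation and whether it applies to every arm. As long as the test depends on the arm, its own baseline remains after allocation.

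State which visit supplies the pre value for GVS versus control. If it is visit 3, this change does not protect that contrast.

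Moving the allocation adds no test and leaves the sample size unchanged. The downside is less lead time to form the videoconference groups and to deliver step benches, lamps and other equipment. If the reconciliation ends with all arms taking the VO2 peak test, that would add a test for the 25 GVS participants.

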**Figure 1 fig1:**
[figure not shown]
Participant’s flow chart. **(A)** The first part of participant’s flow chart: PET and PET+BLE interventions; **(B)** the second part of participant’s flow chart: GVS intervention. PET, Physical Exercise Training; BLE, Bright Light Exposure; HE, Health Education; GVS, Galvanic Vestibular Stimulation.

Sleep, circadian rhythms, physical and motor fitness, cognitive, QoL, and mood measurements will be assessed during visits 2, 3, and 4, by researchers in our laboratory. The VO_2_ peak test will be performed during visits 2 and 3 only for PET, PET + BLE, and control groups (not for the GVS group, which will not engage in physical exercise) and will allow the exclusion of participants with cardiac disorders. These tests will be conducted by cardiologists at the sports medicine departments of the local hospital of CHU in Caen. The content of all assessments is described in Figure 1.

